## Abstract

**Background:**

Patients living in nursing homes have increased aging, comorbidity, spending on health resources and mortality. High drug use is associated with an increased risk of falls, disability, and death. It is estimated that 20%–50% of inappropriate medications are consumed in the elderly.

**Objective:**

This abstract outline the study protocol for evaluating the effectiveness of a pharmaceutical intervention designed to optimize medication use among nursing home residents, with a particular focus on reducing drug-related problems (DRPs) and minimizing polypharmacy.

**Hypothesis:**

The pharmaceutical intervention led by a primary care pharmacist and based on systematically reviewing the pharmacotherapeutic plans of patients admitted to nursing homes will effectively improve the quality and safety of treatment plans.

**Methodology:**

Pre-post, quasi-experimental intervention study with a control group and prospective 3-month follow-up of a cohort of patients in nursing homes. The intervention consists of a clinical review of the pharmacotherapeutic plan carried out by the pharmacist and subsequently agreed upon in the pharmacotherapeutic advisory committee.

**Determinations:**

The study variables will be evaluated at baseline and 3 months post-intervention. The outcome variables are drug-related problems and polymedication.

**Statistical analysis:**

Percentage change will be measured before and after the intervention. Descriptive statistics will be performed for quantitative variables such as qualitative and comparison of means and proportions.

**Expected results:**

Decreasing 10% DRPs in terms of number of DRPs per patient as well as the proportion of patients experiencing DRPs. Reducing 10% polymedication in terms of the number of drugs per patient as well as the number of polymedicated patients.

**Applicability and relevance:**

This study will expand the collaboration between the pharmacy and primary care physicians, promoting the continuum of care, strengthening the safety culture, and improving prescribing habits.

**Ethics:**

The protocol was approved by the Research Ethics Committee of the Jordi Gol Primary Care Research Institute (IDIAP), Barcelona, 22/191-EOm.

**Trial registration:**

clinicaltrials.gov, NCT05944328 Registered.

## Introduction

Drug-related problems (DRPs)—including potentially inappropriate medications (PIMs), medication errors (MEs), and adverse drug events (ADEs)—represent a major and avoidable public health issue (Meyer-Massetti et al., 2018). DRPs are considered the most prevalent cause of iatrogenesis worldwide, particularly among frail patients. There is robust evidence indicating that DRP-related morbidity is a largely preventable health burden (Ruiz-Ramos et al., 2021).

Approximately 38% of emergency department visits are associated with an DRP, of which more than 70% are considered preventable (Baena et al., 2014; Patel and Zed, 2002). Additionally, DRPs account for 5%–10% of hospital admissions and 21% of readmissions (Nivya et al., 2015). Risk factors for DRPs include advanced age, polypharmacy, comorbidities, anticoagulant use, and cognitive impairment, placing individuals over 65 years at particularly high risk (Zhou et al., 2018).

Polypharmacy may be defined qualitatively as the use of more medications than are clinically appropriate, and quantitatively by a numerical threshold. It is commonly defined as the chronic use of five or more medications, while the risk increases significantly with ten or more prescribed drugs, warranting closer clinical attention (Duerden et al., 2013; Gnjidic et al., 2012). Several studies have demonstrated a strong association between the number of medications and the likelihood of ADEs, with the risk rising from 6% with two drugs, to 50% with five, and nearly 100% with eight or more medications (Chumney and Robinson, 2006).

A recent study has linked polypharmacy with an increased risk of falls, with the prevalence of fall risk being twice as high in patients taking 10 or more medications, particularly with antipsychotics and sedative-hypnotics (Turegano et al., 2019). Residents in nursing homes consume approximately four times more medications than community-dwelling individuals with similar clinical profiles (Walley and Scott, 1995). This high level of prescribing often results from the uncritical application of clinical practice guidelines without individualizing therapeutic decisions based on the patient’s benefit–risk profile (Holmes et al., 2006).

Consequently, DRPs—particularly PIMs—are highly prevalent in nursing home residents (Leguelinel-Blache et al., 2020). A PIM is defined as a prescription in which the potential risks outweigh the expected benefits, especially when safer alternatives exist (Delgado-Silveira et al., 2015). It is estimated that approximately 40% of prescriptions in nursing home residents may be inappropriate (Leguelinel-Blache et al., 2020). Various studies have found that 15%–50% of residents are exposed to at least one PIM, with an average of 2.2–4 DRPs per patient (Forsetlund et al., 2011).

Vink et al. (2011) found that pharmacists were able to identify DRPs that other healthcare professionals did not detect. Most DRPs were related to suboptimal therapies or unnecessary medications (Monzón-Kenneke et al., 2021). Comprehensive medication review is a patient-centered approach aimed at optimizing drug therapy and improving clinical outcomes by ensuring that each medication is indicated, effective, and safe for the patient’s current condition (Roth McClurg et al., 2024).

In recent years, pharmacist-led medication review programs have been implemented in nursing homes. Interventions conducted by multidisciplinary teams (physicians, nurses, and pharmacists) have shown reductions in healthcare costs and iatrogenic risks, although results have been heterogeneous and sometimes difficult to interpret. A recent meta-analysis suggests that pharmacist-led deprescribing programs in nursing homes can reduce the prevalence of PIMs by 59% (Kua et al., 2019). Another meta-analysis found that pharmaceutical interventions in nursing homes resulted in a 43.8% reduction in the incidence of falls (Lee et al., 2019).

Aligned with the principles of the Catalan national strategy for primary and community care 2016–2020 (Generalitat de Catalunya, 2015), the Interdepartmental plan for health and social care (Departament de Salut, 2019) was developed to provide integrated, person-centred care to nursing home residents. This plan proposes an efficient pharmaceutical care model that enhances medication safety, quality of life, and health outcomes, with the explicit goal of integrating the pharmacist into the multidisciplinary care team.

As part of the Program for chronic care management developed by the Catalan department of health (Departament de Salut, 2015), the Basic guide for medication management in chronic patients was published (Departament de Salut, 2013). This guide outlines a methodology for treatment optimization through patient-centred, multidisciplinary medication review procedures involving reconciliation, review, deprescribing, and adherence strategies.

In this context, the Primary care directorate of the Camp de Tarragona region (Catalan health institute) oversees 24 nursing homes linked to 20 primary care teams, serving a total of 1,928 residents in 2022. Within this policy framework, a pharmaceutical care program was launched in nursing homes with the aim of reducing DRPs and improving medication safety.

This abstract presents the study protocol, which aims to evaluate the effectiveness of a pharmacist-led intervention to optimize medication use in nursing home residents.

### Hypothesis

This study hypothesizes that a pharmacist-led intervention involving the systematic review of pharmacotherapeutic plans in nursing home residents will improve the quality and safety of their medication regimens.

## Methods

### Objective

The primary objective of this study is to evaluate the effectiveness of a structured pharmaceutical intervention based on the review and optimization of pharmacotherapeutic plans to improve their appropriateness for individuals residing in nursing homes.

Specifically, the study aims to determine, over a 3-month period, the effectiveness of the program in (Meyer-Massetti et al., 2018): reducing drug-related problems (DRPs), as measured by the number of DRPs per patient and the proportion of patients with DRPs, and (Ruiz-Ramos et al., 2021) reducing polypharmacy, in terms of the average number of medications per patient and the number of patients exposed to polypharmacy.

### Design

This is a quasi-experimental study using a non-randomized cluster assignment of patients (nursing homes) into two groups: (a) an intervention group receiving a structured review and optimization of pharmacotherapeutic plans, and (b) a control group receiving usual care based on standard clinical practice (Figure 1).

**FIGURE 1 F1:**
[figure not shown]
Study development algorithm: centre allocation, sampling and monitoring.

### Study location and sample

The study will be conducted in the 24 nursing homes served by primary care teams from the Primary care directorate of Camp de Tarragona (Catalan health institute).

Inclusion criteria: individuals aged 65 years or older, on pharmacological treatment with at least one medication, for a period longer than 3 months. Exclusion criteria include: patients hospitalized at the time of the review, those in end-of-life care, those for whom participation may be deemed potentially harmful by the responsible physician, and patients not covered by the public healthcare or pharmacy system.

### Assignment to study groups

Clustering was defined at the level of the nursing home to minimize the risk of contamination, as residents within the same facility are typically treated by the same medical and care teams. Assigning entire centers to either the intervention or control group also facilitated the coordinated implementation of the structured medication review process and aligned with the organizational routines of the participating facilities.

Assignment to either the intervention or control group will be based on convenience within the context of implementing the pharmaceutical review program in the study area. The first 12 nursing homes in which the program is implemented will be allocated to the intervention group, with the remaining nursing homes forming the control group. The comparability of the groups will be ensured in terms of nursing home characteristics (geographical location, size, organizational and healthcare features) and patient profiles (sociodemographic and clinical variables.

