These recommendations are then evaluated and agreed upon by a committee composed of the responsible physicians and the pharmacist. Consensus-based proposals are subsequently discussed with the patient or their legal representative, leading to a shared decision. Recommendations may be accepted or rejected.

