### Usual care (control group)

In the control nursing homes, pharmacological treatments will be managed following standard procedures. Typically, primary care physicians only authorize and prescribe treatments proposed by nursing home physicians, with limited involvement in ongoing medication management. However, they have access to electronic clinical decision support tools aimed at improving prescribing quality. These include the self-audit tool which detects therapeutic duplications, polypharmacy, contraindications, and inappropriate treatment durations- and the PREFASEG (Safe pharmacological prescription) module, which alerts prescribers to potential interactions, contraindications, and redundancies when initiating new therapies.

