### Statistical method

The main analyses will be by intention to treat, taking into account the patients in each group according to the initial assignment to the study groups, regardless of the compliance with the program by the patient or the responsible physicians, or any other pharmaceutical adequacy intervention that the physicians or patients in the control group may receive.

We will first describe the baseline characteristics of the sample and compare the intervention and control groups to assess baseline comparability. Although the intervention is mainly directed at the prescribing physician through recommendations or suggested changes, outcomes will be assessed at the individual patient level. We will account for potential non-independence of observations arising from patients being managed by the same physician (cluster effect).

Primary outcome variables include: number of DRPs per patient, proportion of patients with DRPs, number of medications per patient, and proportion of polymedicated patients. The effects of the intervention on dichotomous outcomes will be assessed using multilevel mixed-effects logistic regression models (cluster-adjusted), with the odds ratio (95% CI) of the intervention group *versus* control serving as the measure of effect. For continuous variables, we will use linear mixed-effects regression models (cluster), calculating differences between adjusted means (95% CI) between the intervention and control groups. Statistical significance will be set at p < 0.05.

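### Assigning by nursing home does not address contamination between homes that share a primary care team, and the roll-out rule does not keep such homes in one arm

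*Protocol article*

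**What the plan says.** Under Assignment to study groups, the article states: "Clustering was defined at the level of the nursing home to minimize the risk of contamination". The reason follows directly: "as residents within the same facility are typically treated by the same medical and care teams". The allocation rule in the same section is order of implementation: "The first 12 nursing homes in which the program is implemented will be allocated to the intervention group". The remaining homes are the controls. No rule refers to teams or physicians who serve more than one home.

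The Introduction says that the directorate "oversees 24 nursing homes linked to 20 primary care teams, serving a total of 1,928 residents in 2022". Study location and sample uses all 24 homes.

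On how the intervention acts, Statistical method says that "the intervention is mainly directed at the prescribing physician through recommendations or suggested changes", and Intervention says that proposals are "evaluated and agreed upon by a committee composed of the responsible physicians and the pharmacist". Under Usual care, "primary care physicians only authorize and prescribe treatments proposed by nursing home physicians", and the sentence goes on to describe their part in ongoing medication management as limited.

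The limitations in the Discussion cover selection bias and information bias. They do not mention contamination.

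**The concern.** Assigning whole homes stops spread between residents of one home. It does nothing about spread between homes served by the same prescribers. The intervention works through prescribers, and there are fewer teams than homes, so this second route has to be closed by the allocation rule or handled in the analysis. The article does neither. Statistical method itself treats the shared physician as a source of dependence between patients, so the link is recognised for the analysis but not for allocation.

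If a physician sat on the review committee for an intervention home and also prescribed in a control home during the same 3 months, some of the change in practice could reach the control residents. The control arm would improve, the difference would shrink, and a programme that works could look weaker than it is. Modelling the cluster effect corrects the standard error. It does not undo a shift in the control mean.

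**Working it through.** **Step 1: the plan's own figure.** Inputs from Sample size: 0.50 against 0.40, two-sided alpha 0.05, power 0.80, 12 clusters per arm, ICC 0.001, 10% loss.

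- Per arm without clustering: [1.96·√(2·0.45·0.55) + 0.842·√(0.50·0.50 + 0.40·0.60)]² / 0.10² = 388 after rounding up.
- Design effect at about 33 evaluable residents per home: 1 + (33 − 1)·0.001 = 1.032.
- 388·1.032 = 400.4 per arm; /12 = 33.4 per home; /0.9 = 37.1. The article states 37, so the figure reproduces.
- With 37·0.9 = 33.3 evaluable residents per home, the effective n per arm is 12·33.3 / (1 + 32.3·0.001) = 387 and power is 0.80. The plan has no slack.

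**Step 2: how many homes share a team.** Inputs: 24 homes, 20 teams (Introduction).

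- If 20 or more homes each had a team to themselves, all 20 teams would be used up and the other homes would have none. So at most 19 homes are unshared, and at least 24 − 19 = 5 share a team.
- Assume that each home has exactly one team and every team has at least one home. There are then 24 − 20 = 4 surplus homes. The most sharing homes is 8 (four teams with two homes each). The most control homes that can share a team with an intervention home is 4 of 12.
- If a home can be linked to more than one team, the upper limit of 4 no longer holds. The lower limit of 5 does.

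For illustration only: if four teams had two homes each and the order were random, the expected number of split pairs would be 4·12/23 = 2.1 and the chance of no split about 5%. The real order is by convenience, so this is not an estimate.

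**Step 3: what carry-over would do.** The documents give no carry-over figure, so a range is assumed. With k affected control homes of equal size, each taking up a fraction f of the effect:

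control proportion p = 0.50 − (k/12)·f·0.10; difference d = p − 0.40.

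Power = Φ[(d − 1.96·SE₀)/SE₁], with effective n = 387 per arm, SE₀ from the pooled proportion and SE₁ from the two separate proportions.

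Worked case, k = 4 and f = 0.5: p = 0.4833, d = 0.0833, SE₀ = 0.0357, SE₁ = 0.0356; (0.0833 − 0.0700)/0.0356 = 0.38; power = 0.65.

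| Affected control homes | Carry-over | Control proportion | Difference (points) | Power |
|---|---|---|---|---|
| 0 | – | 0.500 | 10.0 | 0.80 |
| 1 | 25% | 0.498 | 9.8 | 0.78 |
| 1 | 50% | 0.496 | 9.6 | 0.77 |
| 2 | 50% | 0.492 | 9.2 | 0.73 |
| 4 | 25% | 0.492 | 9.2 | 0.73 |
| 4 | 50% | 0.483 | 8.3 | 0.65 |
| 4 | 100% | 0.467 | 6.7 | 0.46 |

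The last row is an outer bound: four control homes with no pharmacist review would gain the full effect.

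**The case against.** The case against is substantial.

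- **A shared team is not a shared prescriber.** The committee is made up of the responsible physicians, not the whole team. A team may have several physicians who each cover a different home, and roll-out may have kept linked homes together. This stands: the count proves shared teams and nothing further.
- **The route may be narrow.** In control homes the nursing home physicians propose treatment, and primary care physicians have limited involvement. The pharmacist's review of each treatment plan, which finds many of the problems, reaches control homes only after follow-up. Control prescribers also already have alert tools. This stands too, and it argues for small carry-over.
- **The stated reason is sound as far as it goes.** Sharing of care teams within a home is a valid reason not to assign residents individually. The gap is that this reason is offered for contamination in general and is silent about spread between homes.
- **The home-to-team map may be in a fuller document, and the allocation figure is not shown.** That is fair, and the missing map is not the point here. The point is that the published rule sorts homes by start order alone.

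A reader might go further and infer that the intervention trains physicians who then prescribe in control homes, so that dilution is certain. The documents do not support that. They describe committee agreement on proposals for individual patients and no training, they place no physician in both arms, and they give no carry-over rate.

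**Conclusion.** The point holds as a gap in the allocation rule and in the argument given for it, not as a demonstrated bias. It is certain, from the stated counts, that at least 5 homes share a team, and nothing in the published rule keeps such homes in one arm. It is not known whether any team or physician is split across arms, or how much would carry over.

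If there is carry-over, its direction is towards no effect. Its size is bounded only under assumptions: one team per home, homes of equal size, the plan's ICC of 0.001, and an assumed uptake. Within 1 to 4 affected homes and 25–50% uptake, the loss is 0.2 to 1.7 of the 10 points, with power of about 0.78 to 0.65. The 0.46 figure is the extreme and should not be read as a forecast. If roll-out kept linked homes together, the loss by this route is zero. The point is worth acting on because the remedy is cheap and the sample size leaves no margin.

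**What to change.** 1. Where the roll-out order is still open, add to Assignment to study groups: *All nursing homes linked to the same primary care team, or sharing a physician, are allocated to the same group.*
2. Where linked homes are already split, prespecify a sensitivity analysis that leaves out control homes sharing a team or physician with an intervention home. The past tense used for data collection, and for the later delivery of the intervention to control homes, suggests that this may be the only option left.
3. Limit the contamination statement in Assignment to study groups to spread within a home, and add spread between homes to the limitations in the Discussion.

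Cost: a few sentences and one extra analysis. Keeping linked homes together may make the arms slightly unequal in number of homes. The sensitivity analysis uses fewer control homes, up to 4 fewer with one team per home, so it is less precise and should be read alongside the main result, not in place of it.

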## Discussion

This is a pragmatic study that integrates an evaluation framework into the implementation process of a new medication review and optimization program in nursing homes. Although the intervention is well-established and supported by scientific evidence, the main goal of this study is to assess its utility and effectiveness in routine clinical practice.

A novel aspect of the program is the expanded role of the clinical pharmacist as a support and advisor to general practitioners in identifying drug-related problems and proposing solutions. This approach aligns with healthcare improvement initiatives in nursing homes, involving a redefinition of professional roles and the promotion of multidisciplinary teamwork (Departament de Salut, 2019).

This study will have certain limitations that should be considered when interpreting the results. One of the main concerns will be the non-random allocation of care homes to the intervention and control groups, which was based on convenience and collaboration feasibility within the framework of the local pharmaceutical review program. Although this approach is justified for practical reasons, it may introduce a potential risk of selection bias. To minimize this, we will ensure that the two groups are comparable at baseline in terms of care home characteristics (e.g., geographical location, size, and organizational structure) and patient-level variables (e.g., sociodemographic and clinical profiles, as well as the quality of pharmacotherapeutic plans). Any residual imbalances will be addressed through appropriate statistical adjustments during the analysis.

The fact that the assessment is neither blind nor independent introduces a potential risk of information bias, as the pharmacists responsible for implementing the intervention also carry out the outcome assessments in the intervention group. However, this risk is mitigated by the fact that outcome data will be obtained directly and systematically from the electronic health records, based on structured variables that are not modifiable by the assessors. Due to resource limitations, it is not feasible to separate intervention and assessment roles, and this potential bias should be considered when interpreting the study results.

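### The order in which the programme is implemented decides each home's arm, so no home-level assignment stands apart from receiving it, and comparability cannot be ensured as promised

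*Protocol article*

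**What the plan says.** The protocol article declares its design openly in Design: "This is a quasi-experimental study using a non-randomized cluster assignment of patients (nursing homes) into two groups". Assignment to study groups gives the rule: "Assignment to either the intervention or control group will be based on convenience", and then "The first 12 nursing homes in which the program is implemented will be allocated to the intervention group". All other homes form the control group. The Discussion describes the same allocation as one "which was based on convenience and collaboration feasibility within the framework of the local pharmaceutical review program".

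On balance, Assignment to study groups says "The comparability of the groups will be ensured in terms of nursing home characteristics" and extends this to patient profiles. The Discussion repeats the promise: "we will ensure that the two groups are comparable at baseline in terms of care home characteristics". It adds that residual imbalance will be handled by statistical adjustment. Statistical method is more modest and says the authors will "compare the intervention and control groups to assess baseline comparability".

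On the analysis set, Statistical method specifies intention to treat, "taking into account the patients in each group according to the initial assignment to the study groups", whatever the compliance of patients or responsible physicians and whatever other medication interventions controls receive. Ethical aspects says control homes received the programme after follow-up, under a planned rollout.

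**The concern.** There are two linked problems.

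First, the rule lets implementation define the label. Intention to treat needs an assignment that exists before, and separately from, receipt of the intervention. The text gives no list or date that fixes the 12 homes, so a home meant to be early that stalls has no status except control. Its residents would not count against the programme, and the next home in the order would enter the intervention arm. That route runs in the programme's favour. It matters here because the Discussion states the aim as effectiveness in routine practice, where failure to start is part of the answer.

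Second, ensuring comparability is more than the rule can deliver. If easier collaboration brings a home in earlier, the arms may differ in readiness to act on medication advice. Readiness plausibly affects the outcome, because the Intervention section requires proposals to be agreed with the responsible physicians and allows them to be rejected. Readiness is not among the characteristics on which comparability is promised.

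**Working it through.** **The plan's own figure.** Inputs from Sample size: 0.50 versus 0.40, two-sided alpha 0.05, power 0.80, 12 clusters per group, ICC 0.001, 10% loss.

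- Per arm without clustering: n = [1.96·√(2·0.45·0.55) + 0.8416·√(0.25 + 0.24)]² / 0.10² = 388 (rounded up).
- With m evaluable residents per home: 12m = 388·[1 + (m − 1)·0.001], so m = 388·0.999 / (12 − 0.388) = 33.4.
- With 10% loss: 33.4 / 0.90 = 37.1, against 37 stated.

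The figure reproduces. The allocation rule does not alter this arithmetic, and the calculation contains no allowance for confounding from non-random assignment.

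**Weight of one home.** Each arm has 12 × 37 = 444 planned participants. One home is 37/444 = 1/12 of an arm.

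**Does a home-level assignment exist before receipt?**

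1. Assignment to study groups makes a home an intervention home by its place among the first 12 implementations.
2. Statistical method analyses by initial assignment and names two sources of non-compliance, patients and responsible physicians. Both arise after a home has been labelled.
3. A home that is scheduled but never started has not been labelled under step 1, so step 2 does not reach it. It becomes a control because it is not among the first 12.
4. Ethical aspects mentions a planned rollout, but Assignment to study groups does not tie the arms to that plan.

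**Can comparability be ensured?**

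1. Study location and sample uses all 24 homes, so there are no spare homes to match or select from.
2. The split is 12 and 12 by order. No stratification, matching or balancing of that order is described.
3. Sampling of residents may occur: 24 × 37 = 888 participants are needed from 1,928 residents, about 1,928/24 = 80 per home. Sampling within homes could affect patient profiles. It cannot change a home's location, size or organisation, which are the first things promised to be comparable.
4. Statistical method compares the groups after assignment, which describes balance and does not create it.

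Set side by side, the article promises to ensure balance, uses a convenience rule that has no means of doing so, and plans an analysis that only assesses it.

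**The case against.** The best defence is that the order may have been fixed in advance. The Intervention section places the review in the standard service portfolio, delivered by the territorial pharmacy unit, and Ethical aspects calls the rollout planned. The service could have weighed location and size when setting the order. Figure 1, which covers centre allocation, is not available here, so the absence of a list cannot be treated as proven. This stands in part: the text leaves room for a prior schedule but does not make it the basis of assignment.

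The selection problem is also disclosed. The article calls the design non-randomised, names selection bias as a main limitation and promises adjustment. That stands too. Choosing a quasi-experimental design is not an error, and the point here is not that the design was concealed.

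A reader might infer three stronger things that the document does not support:

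- **That the rule contradicts intention to treat.** It does not. Once homes are labelled, residents can be analysed as labelled, and rejected recommendations in a started home still count against the programme. The gap is confined to homes scheduled but not started.
- **That reluctant homes were in fact replaced by readier ones.** No such event is reported, and the article says control homes received the programme after follow-up.
- **That the bias can be expressed in percentage points.** That would need a number of non-starting homes, which the document does not give. It would also set the effect where the programme is implemented against the effect of being scheduled for it, which are two different estimands.

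**Conclusion.** The point holds in a limited form. As worded, the intervention arm has no definition separate from receipt of the programme, so intention to treat protects against non-compliance by patients and physicians but not against a home failing to start. The promise to ensure comparability is not supported by the stated rule, and the analysis section itself commits only to assessing balance.

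Each home that failed to start would shift one twelfth of an arm. How many did so, if any, is unknown, so the bias is left unquantified. The reference to feasibility of collaboration makes dependence on readiness plausible but does not establish it. The conclusion rests on the visible text and on the assumption that Figure 1 and the unseen full protocol do not already tie the arms to a dated list. If they do, the first part is settled by citing that list, and only the wording on comparability needs correcting.

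**What to change.** 1. In Assignment to study groups, set a dated list of the 12 intervention and 12 control homes before baseline collection. If a planned rollout schedule exists, take the list from it and state when it was fixed.
2. In Statistical method, say that every home is analysed by that list whether or not it starts on time.
3. In Assignment to study groups and the Discussion, replace the promise to ensure comparability with a statement that it will be assessed and adjusted for. Use the home-level variables (location, size, organisation) and patient-level variables (sociodemographic and clinical profile) already named, and include the baseline outcome.
4. Optionally, if the order is still open, choose it at random among 12/12 splits balanced on location, size and organisation. This would change the declared design, so it is not needed to resolve the point.

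**Cost.** Items 1 to 3 need one dated document and edits to three sections, with no additional homes, staff or residents. A listed home that starts late or not at all will dilute the estimate, which suits the article's stated aim of effectiveness in routine practice. Adjustment will not remove a difference in readiness that is not measured, so the limitation in the Discussion should stay. Item 4 costs the pharmacy unit some freedom in scheduling and would alter a protocol that already has ethics approval and registration.
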